## Methods and design

### Overview

The Circle of Security Study in Hamburg represents a clinically pragmatic form of prevention and intervention, performed in a RCT. The study is comparing two mother-infant treatment groups, assigned to COS or TAU as the control condition, in the outpatient unit at the Department of Child and Adolescent Psychiatry, Psychotherapy, and Psychosomatics at the University Medical Center of Hamburg. The recruitment, baseline and follow-up assessment of mother-infant dyads started in January 2010 and will end in April 2014. Participants were recruited from among those mothers visiting the outpatient unit who volunteered to take part, and after having given their informed consent, entered the baseline assessment for this study. Mothers with mental disorder and their infants attending the outpatient unit were referred to the unit from other medical/mental health services they had been accessing from different areas of Hamburg, an urban city with a population of approximately 1.8 million inhabitants.

### Aims and hypothesis

The primary aim of this study is to evaluate the efficacy of COS versus TAU in mothers with mental disorder and their infants in promoting attachment security in the child under standard clinical outpatient conditions. More specifically, the goal of the study is to determine whether COS intervention results in more securely attached infant–mother dyads than the control condition (TAU). The primary hypothesis is that the COS intervention will bring about a higher rate of securely attached children after treatment and at follow-up (when the children are aged 16–18 months) than TAU. Secondary hypotheses being tested by the study are that i) COS intervention will lead to an increase in sensitive behavior in mothers, ii) COS intervention will result in an increase in mothers’ ability to mentalize, and iii) COS intervention will improve mothers’ state of mind with regard to their own attachment, relative to TAU.

### Participants

All eligible mother-infant-dyads seeking mother-infant treatment were invited to participate in this study, and were entered into the baseline assessment after both parents having given their informed consent. The inclusion criterions were again verified, and the mother-infant dyads then randomly assigned to the treatment arms. Demographic information, such as socioeconomic status, as well as age, education, and treatment history of the mothers were assessed at baseline. All mother-infant dyads were German-speaking residents of the greater Hamburg area.

#### Eligibility criteria

The inclusion criteria are child age 4–9 months and mothers’ being a fluent speaker of German. The exclusion criteria are child autism and early retardation or a primary ICD-10/DSM-IV diagnosis of substance abuse, schizophrenia, intellectual impairments (IQ < 80), or suicidal ideation and/or recent suicide attempt in mothers. No other exclusions were made in order to ensure that a full and representative spectrum of mentally ill mothers with infants attending our outpatient unit for was included.

### Interventions

This trial aims to evaluate the efficacy of the COS group treatment protocol compared to TAU as the control condition. The COS group intervention consisted of 20 90-minute sessions delivered weekly on Tuesday afternoons, plus one additional session of 120 minutes with the fathers or close family members on one Saturday. The TAU condition was delivered at different levels of intensity, as needed by the mothers. Mothers assigned to either of the treatment arms were permitted to receive psychopharmacological medication as part of their adult psychiatric treatment to manage clinical symptoms, as well as individual psychotherapy and/or other psychosocial services.

#### Circle of Security (COS) intervention

The Circle of Security (COS) intervention
[64,67] was designed to alter developmental pathways for at-risk parents and their children. In the current study, COS was only used with mothers, except for the single additional session with fathers/family members. It was conceptualized as a psychodynamically oriented, psychotherapeutic and community-based parenting program and is considered to be evidence-based in the USA. The COS is a treatment based on groups of six individuals. The group intervention focuses on the caregiver and his/her relational capacities in providing child–parent attachment security. The COS manual (unpublished) draws upon the work practiced in Early Head Start and Head Start programs in the USA and was developed by the originators
[68] at the Marycliff Institute in Spokane, WA. The COS therapists of the current trial underwent an intensive 10-day training in COS assessment and treatment organization at the Marycliff Institute in preparation for this study.

Prior to the beginning of the group therapy, a thorough diagnostic assessment of the interactions between mother and infant in various situations was performed, during which attachment and explorative behaviors were activated. Additionally, an interview with regard to caring for the child (the “Circle of Security” Interview;
[69]), as well as an attachment interview (Adult Attachment Interview, AAI;
[70]) were conducted with the mother. With the “Circle of Security” model as a foundation for intervention, an assessment of the relationship between mother and child was prepared with the help of video recordings and both interviews. From this assessment, the maternal core difficulty (termed the “linchpin struggle”) and the preferred (unconscious) defense strategy against potential threatening or uncomfortable emotions (procedural) or cognitions (termed “shark music”) connected with the attachment and autonomy needs of the child, were deduced. An individual treatment plan was formulated for each mother-infant-dyad,. This treatment plan contained a sampling of video sequences, which were used throughout the therapeutic process in order to acquaint the mother with her “linchpin struggle” whilst taking the mother’s “core sensitivity” and “shark music” into account. The “core sensitivity” describes an integral aspect of the personality
[71,72], which represents the emotional organization of relationships and the basis for defensive processes in the parent–child interaction. The need for relationships and the fear of the loss of these relationships or separation play central roles in this. Each mother’s idiosyncratic manifestation of this complex interplay was taken into consideration in the selection of the video sequences.

Every therapeutic group consisted of six women. Six groups were planned and realized for this trial. The infants did not participate in group sessions, and childcare was provided for them while the mothers were in sessions.

The treatment manual, which was designed for parents with children aged 0–5 years, combines psycho-educational and therapeutic modules (e.g., video analyses in the group), focusing on attachment, exploration, communication and affective experiences between parent (in this study, mother) and child, aiming to help the mothers to elaborate their strengths and struggles in order to create a haven of safety and a secure base for their children. Guided by the treatment manual, there is a shift from predominantly observing behavioral and affective cues of both mother and child to gaining more insight into maternal thoughts and feelings and their defensive nature (“shark music”) with regard to the attachment and autonomy needs of the children, with the goal of overcoming their impact on child-mother attachment formation and maternal sensitivity. This is intensified by showing video segments of the “linchpin struggle” of each mother-infant dyad.

The 90-minute-COS group sessions took place weekly. Two therapists facilitated each group. Treatment adherence and integrity in this study was assured by weekly supervision of the therapists with [name], one of the originators of the COS intervention.

#### *Treatment* a*s usual (TAU)*

As a control condition, TAU was provided to mothers with their infants within the child and adolescent psychiatric outpatient unit. TAU consisted of standard treatment, which may have involved case management or counseling for the mothers. The treatment was offered by two child and adolescent psychiatrists and psychotherapists with a theoretical blend of psychodynamic and behavioral training in therapeutic work with mentally disordered mothers and infants. The focus was on the mother, the child, and/or the mother–child relationship; fathers were sometimes included. Each treatment session typically lasted 50 minutes. The intensity and length of treatment depended on the specific needs of each mother–infant dyad, and treatment was terminated by the mothers. The exact number of treatment sessions was recorded. Mother–infant dyads with particular needs were referred for additional services (e.g., social support services, family midwives). Most of the mothers attending the outpatient unit had seen an adult psychiatrist to confirm their diagnosis and further treatment indications at least once, at the beginning of treatment. At the time of follow-up, treatment satisfaction will be assessed for all mothers in the COS and TAU groups.

### Assessment and outcomes measures

All measures of pre- and post-assessment are listed in Table 
1.

**Table 1 T1:** Assessments administered at baseline and follow-up throughout the trial

**Time point**	**SSP**	**MBQ-S**	**DIP**	**AAI**	**AAI-RF**	**PRFQ-1**	**SCID-I,-II**	**BDI**	**SCL-90**	**PSI**	**DERS**	**CBCL**	**FBB-E**
**Baseline**													
Child age 4–9 months	**-**	√	√	√	√	√	√	√	√	√	√	√	**-**
**Follow-up**													
Child age 16–18 months	√	√	√	√	√	√	**-**	√	√	√	√	√	√

#### Primary outcome

##### Child attachment

The primary outcome of the current study is child attachment security (vs. insecurity). In attachment research, the Strange Situation Procedure [SSP; 22] is the most widely used and well-validated experimental paradigm for assessing the quality of the child’s attachment to a parent in infancy. The ratings for attachment qualities will be done by two trained and reliable coders blind to treatment allocation. The child’s attachment behaviors will be rated for classification into secure-B, or into avoidant-A or ambivalent-C as insecure-organized attachment qualities, according to the standard criteria described by Ainsworth
[22], and for classification into insecure-disorganized/disoriented-D attachment qualities, according to the Main and Solomon
[35] coding system.

#### Secondary outcomes

**Mini-MBQS** - Maternal sensitivity. The revised mini-Maternal Behavior Q-Sort (mini-MBQS) for video coding
[73], a 25-item observational coding instrument, is used for measuring the quality of maternal sensitive behavior. The q-set items relevant to attachment are mapped onto a prototypically sensitive mother
[74]. During the mini-MBQS sorting process, coders systematically evaluate and sort each of the 25 q-set items into one of the five categories (i.e., “most like mom”, “like mom”, “unlike mom”, “neither like nor unlike mom, “least like mom”) respectively, based upon behavioral observations of videotaped interactions between mother and child. Correlation scores are calculated, varying from -1.0 (least sensitive or responsive) to 1.0 (prototypically sensitive or responsive) between the observer sorts and a criterion sort for the prototypically sensitive and responsive mother, which is provided by the developers of the instrument. In this trial, mini-MBQS data are derived from videotaped 5-minute free play and 5-minute book reading interactions at baseline and follow-up, each coded by two independent raters blind to treatment allocation.

**DIP** - The Disconnected and extremely Insensitive Parenting rating procedure
[75] is used to identify extreme insensitivity and/or disconnection in the mother. The DIP captures those maternal behaviors that are most likely related to poor child attachment outcomes
[75]. Disconnected behavior and extreme insensitivity are rated on a scale ranging from 1 to 9, indicating an incrementally increasing display and/or prolonged duration of such behaviors. For pre- and post-assessment, the DIP is administered for the same 5-minute-interaction episodes (free play, book reading) as the mini-MBQS by two independent raters who each have undergone DIP rating and reliability procedure training.

**AAI** - The Adult Attachment Interview and its respective scoring and classification system
[70,76] represent the “gold standard” for classifying maternal state of mind with regard to attachment (as F, Ds, E, U). In the current trial, it is administered at baseline and follow-up. Mothers classified as unresolved (U) with regard to loss or trauma will also be assigned into a secondary best-fitting organized attachment category. The interviews will be transcribed verbatim and coded by two reliable raters who are blind to treatment allocation.

**RF -** The Reflective Functioning (RF) scale of the AAI
[77] is utilized to measure maternal mentalizing, which is defined as the capacity of the mother to reflect upon her own self and close others in terms of intentional mental states. The RF allows for overall ratings of reflective functioning on a nine-point scale ranging from 1 (lacking RF) to 9 (exceptional RF), with two additional RF scores indexing the absence of mentalizing, that is, -1 (negative RF), 0 (lacking RF). RF-ratings will be performed on the AAI obtained at baseline and follow-up by two independent raters blind to treatment allocation.

**PRFQ-1 –** The Parental Reflective Functioning Questionnaire-1
[78] is used as an alternative instrument for assessing RF via self-report. The PRFQ-1 assesses the levels of parental mentalization up to the child’s age of 3 years. It consists of 39 items comprising three subscales prototypically describing high, low, and neither high nor low mentalizing in mothers and fathers. Scoring procedures precepts yield a total score on all three subscales. PRFQ-1 is administered at baseline and follow-up.

**SCID-I** – The German version of the Structured Clinical Interview
[79] for DSM-IV
[80] axis I disorders is used to verify clinical DSM-IV-Axis-I diagnoses. SCID-I interviews were conducted by trained researches at baseline.

**SCID-II** – The German version of the Structured Clinical Interview (SCID-II) for personality disorders is used to identify mothers with probable DSM-IV-Axis II personality disorders. SCID-II interviews were conducted by trained researchers at baseline.

**BDI** – The Beck Depression Inventory
[81,82] is administered to screen for depressive symptoms in the mothers at baseline and follow-up. It consists of 21 items, scaled from zero to three, which are summed to a global score, indicating clinical significance of self-reported depressive symptoms.

**SCL-90-R** – The revised Symptom Checklist by Derogatis
[83] (German version:
[84]) is used to assess maternal psychopathological symptoms. The Global Severity Index, as a sum score of the SCL-90-R, is applied to determine maternal psychopathology at baseline and follow-up.

**PSI** – The Parenting Stress Index
[85] (German:
[86]) is a self-report measure consisting of 120 items for parents with children aged from 0–12 years, capturing child-related and parent-related stress domains. A total stress score is derived, indicating the severity of the subjective burden of parenting. A domain of life events allows for the recording of positive and negative life events. The PSI is measured at baseline and follow-up.

**DERS –** The Difficulties in Emotion Regulation Scale
[87] is a 36-item self-report on clinically relevant emotion regulation difficulties, especially with regard to negative emotions. Items are scored on a 5-point Likert scale ranging from 1 (almost never) to 5 (almost always). The authors have confirmed a six-factor structure of emotion regulation, upon which the DERS is based; and adequate internal consistency (Cronbach’s α > .80) of these subscales has been established
[87]. For the purpose of this trial, the DERS was translated into German. First, the scale was translated from English to German independently by two translators who then discussed their translations and combined them to form a draft of the questionnaire used in the present study. This draft was back-translated into English by a professional translator. The back-translated version was found to be consistent with the original DERS version. The DERS is applied at baseline and follow-up.

**CBCL** – The Child Behavior Checklist1½**-**5
[88] (German version) is a questionnaire for parents of children aged 1.5-5 years, which is used to assess child behavioral and emotional problems. The items are related to seven problem scales, loading on externalizing, internalizing, and a total score. In the current trial, the CBCL will be administered at follow-up.

**FBB-E** – Fragebogen zur Beurteilung der Behandlung – Eltern
[89] (“A Questionnaire to Evaluate Treatment Satisfaction – Parent Version”) is a well-known German language questionnaire for evaluation and quality assurance of the therapeutic treatment of children, adolescents and their families. The FBB-E assesses how positively or negatively parents evaluate the course and outcome, as well as their personal satisfaction regarding the psychotherapeutic treatment of their children, independent of treatment modality. The FBB-E will be applied at follow-up.

### Randomization

#### Recruitment and baseline procedures

The flow of participants from recruitment through to the end of the study is shown in Figure 
1.

**Figure 1 F1:**
[figure not shown]
Consort diagram describing flow of patients through study.

Identification and initial screening of potential participants were performed by the principle investigator of the study, an experienced clinician in the outpatient unit. Once eligible mother-infant dyads were identified, they were informed about the trial and invited to participate. Both custodial parents had to give their informed consent for the baseline assessment, which was performed by trained research staff over several sessions. After completion, the researcher confirmed whether each mother met diagnostic and additional inclusion criteria. If they did, they were randomly assigned to one of the two treatment arms (COS or TAU). Once consent to treatment and post-assessment of both parents had been obtained, a trial ID was assigned. Depending on the natural flow of patients a COS group began once six mother-infant cases had been recruited and assigned. TAU started immediately after random allocation. Follow-up assessment (child age 16–18 months) is continuing.

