#### Randomization procedures and methods to minimize bias

Eligible patients were randomly assigned to the COS intervention or TAU in a ratio of 1:1. An electronic randomization list was generated using Randlist 1.2 as a random generator. Unique randomization numbers were generated to ensure that the study arm assignment was unbiased. Randomization was stratified for two infant age groups (4–6 months vs. 7–9 months) and separate random lists were created for each age group. Block sizes of six to eight were used for the randomization of the treatment arms. The randomization list was generated by the randomization representative and was stored in a password-protected electronic document accessible only by the randomization representative. Each random number was stored in a concealed randomization envelope. After a patient’s eligibility for the study was determined, the next available randomization number was assigned to the patient, in ascending order. To minimize bias that could have arisen from knowledge of treatment allocation, all outcome assessors were blind to treatment allocation and a random sample of outcome measures was re-rated by independent assessors.

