#### Statistical analysis plan

All available variables will be used without missing outcomes being factored in. The analyses are based upon the assumption of ignorable drop-outs. Characteristics of the treatment groups were assessed at baseline.

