### Limitations

The circumstances of this clinical trial necessitated some scientific compromises. One limitation of this trial is that the person who oversaw the implementation of the COS intervention is also the principle investigator. Thus, personal factors (allegiance effects) may limit the generalizability of our findings. In view of the fact that the study sample comprises clinically referred mothers with mental disorders and their infants, it is ethically unacceptable to use a no-treatment control group. Therefore, in the best interest of our patients we have used TAU as the control intervention to which patients are randomized. According to the natural flow of patients attending the outpatient unit, eligible women with infants participated voluntarily, and, having given their informed consent, were randomly assigned to COS or TAU. Thus, our clinical sample varied in terms of psychopathology. There may be a sampling bias, insofar as the mothers with infants attending the outpatient unit might represent a more severely mentally disordered sample choosing to participate in this trial. This may limit the generalizability of the findings, due to sampling bias and a lack of true representativeness. Hence, replication studies or a multi-site trial are necessary. A sample size of N = 80 was determined before any data were collected, based on the assumption of medium effect size and power. For practical reasons, we defined a sample size of N = 72, such that 36 mother-infant dyads were randomly assigned to COS (six COS therapeutic groups) and 36 mother-infant dyads to TAU. Further long-term follow-up measures might be useful to capture positive changes of the intervention that may be attributable to a sleeper-effect
[66] and apparent only at later follow-up stages.

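### As the procedure is described, both parents consent to treatment and follow-up after allocation, so a randomised dyad can leave uncounted; whether any did is not shown

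*Protocol article*

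**What the plan says.** The sequence is in the protocol article under Randomization, Recruitment and baseline procedures (the text after Figure 1). It opens with consent of limited scope: "Both custodial parents had to give their informed consent for the baseline assessment". Baseline assessment over several sessions follows, then a check of the inclusion criteria, then random assignment of dyads that pass. The next sentence reads: "Once consent to treatment and post-assessment of both parents had been obtained, a trial ID was assigned". The section also says that a COS group began once six cases had been recruited and assigned, whereas "TAU started immediately after random allocation".

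Randomization procedures and methods to minimize bias gives the trigger for allocation: "After a patient’s eligibility for the study was determined, the next available randomization number was assigned to the patient, in ascending order". It names eligibility and does not mention consent to treatment.

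Other places that bear on the point:

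- **Participants:** parental consent leads into baseline assessment, and random assignment comes later.
- **Limitations:** eligible women, "having given their informed consent, were randomly assigned to COS or TAU". What that consent covered is not stated. The same section reports 36 dyads assigned to COS and 36 to TAU.
- **Circle of Security (COS) intervention:** "Every therapeutic group consisted of six women", with six groups planned and realised.
- **Statistical analysis plan:** "All available variables will be used without missing outcomes being factored in", with drop-out assumed ignorable.

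**The concern.** Randomisation protects the comparison only if everyone allocated is accounted for in the arm assigned. If the second consent comes after allocation, it can be given or withheld with the arm known.

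The arms ask different things of a family. COS means 20 weekly 90-minute afternoon sessions plus a Saturday session with fathers or close family, after waiting for a group of six to fill. TAU starts at once, at an intensity set by need. Both parents must agree, so family circumstances may also influence who stays. If such factors are related to infant attachment, the dyads remaining in the two arms are no longer comparable. Concealed envelopes and blinded coders do not guard against selection that happens after the envelope is opened.

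The primary outcome makes this matter more. Table 1 schedules the Strange Situation Procedure (SSP) at follow-up only. A dyad that refuses post-assessment has no primary outcome and no earlier value of it.

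**Working it through.** **Order of steps, from the recruitment section**

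1. Both parents consent to the baseline assessment.
2. Baseline assessment is completed.
3. Inclusion criteria are confirmed.
4. The dyad is randomised.
5. Both parents consent to treatment and post-assessment, and a trial ID is assigned.

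The Participants section fits steps 1 to 4. The randomisation section fits step 4 following step 3 with no further condition. A dyad that stops between steps 4 and 5 holds a randomisation number but no trial ID.

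**The plan's own counts**

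Six groups × 6 women = 36, equal to the 36 dyads reported as assigned to COS; 36 + 36 = 72, the reported total. Every assigned COS dyad therefore has a place in a group. This fits no refusals at all. It would also fit refusers not being counted, or being replaced. The text cannot separate these.

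**Possible size of bias**

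The article gives no refusal rate and no secure rate, so all inputs here are assumptions: no true effect, 50% secure in each arm as randomised, a share r of COS dyads refusing, a secure rate p among refusers, and no refusals in TAU.

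Shift in the COS rate among those kept = (0.5 − r·p)/(1 − r) − 0.5

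| r | p | Calculation | Shift (points) |
|---|---|---|---|
| 0.10 | 0.3 | 0.47/0.90 − 0.5 | +2.2 |
| 0.10 | 0.2 | 0.48/0.90 − 0.5 | +3.3 |
| 0.20 | 0.3 | 0.44/0.80 − 0.5 | +5.0 |
| 0.20 | 0.2 | 0.46/0.80 − 0.5 | +7.5 |
| 0.10 | 0.5 | 0.45/0.90 − 0.5 | 0 |
| 0.20 | 0.5 | 0.40/0.80 − 0.5 | 0 |
| 0.10 | 0.7 | 0.43/0.90 − 0.5 | −2.2 |
| 0.20 | 0.7 | 0.36/0.80 − 0.5 | −5.0 |

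**Effect on the test**

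This takes 36 randomised per arm, losses from COS only, and a normal approximation to the two-sided 5% comparison of proportions. With p = 0.2, the type I error is about 5.9% at r = 0.10 and 9.1% at r = 0.20. In the extreme case where no refuser is secure (p = 0), it is about 7.4% and 16.9%. At r = 0.05 it stays near nominal: 5.2% with p = 0.2 and 5.5% with p = 0.

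**The case against.** The order rests on sentence position. The article never says outright that the second consent followed allocation or that parents knew the arm when they gave it. An immediate start of TAU also sits awkwardly with a separate two-parent consent step in between. This stands as a caution. Even so, the only consent placed before allocation covers the baseline assessment, and the randomisation number depends on eligibility alone, so the plain reading remains the one above.

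A reader might infer that the Limitations section contradicts the recruitment section. It does not. It puts consent before randomisation without saying what was consented to. If it means baseline consent, the two agree; if it means full consent, the concern falls away. The wording is ambiguous, which calls for reconciliation.

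A reader might also infer from the round figures of 36, 36 and six groups of six that refusers were replaced. No section describes replacement, and the same figures fit no refusals. Figure 1, the CONSORT diagram, is not in the text available here and may report losses after allocation. The absence of refusal counts is therefore not held against the article.

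A condensed article may leave the analysis-set definition to a fuller document, so its absence alone is not a fault. The point is that the stated sequence opens a gap, and the stated available-data rule does not close it.

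Finally, the upward bias in the illustration follows from assuming that refusers are less often secure. Nothing in the article fixes that direction. This objection stands, which is why the table includes zero and negative shifts.

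**Conclusion.** The concern holds as a risk created by the procedure as written. A dyad can be randomised, refuse with the arm known, and leave without a trial ID or a primary outcome; an available-data analysis under ignorable drop-out does not protect the comparison. The documents do not show that anyone refused, that anyone was replaced, or that the result is biased in favour of COS.

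Under the stated assumptions (no true effect, 50% secure, 10-20% of COS dyads and no TAU dyads refusing), the shift runs from −5.0 to +7.5 points as the secure rate among refusers runs from 70% down to 20%. It is negligible if few refused or if refusers resemble those who stayed. If nobody refused, one sentence saying so settles the matter.

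**What to change.** 1. State when each consent was obtained and what it covered, and bring Participants, Recruitment and baseline procedures, and Limitations into line.
2. Define the randomised population as every dyad given a randomisation number, in its assigned arm, whether or not a trial ID followed.
3. From the randomisation list, report by arm how many dyads were lost between randomisation number and trial ID, and how many, if any, were replaced.
4. If there were any, add sensitivity analyses of the primary outcome: all such dyads counted as insecure, and best and worst case by arm. Use imputation from baseline data only where the consent given allows that use.
5. If any dyad is still to be randomised, obtain both consents before the envelope is opened. Allocation is reported largely in the past tense, so this may no longer apply.

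Neither imputation nor counting losses as insecure should become the primary analysis. The SSP has no baseline value to impute from, and refusers may have agreed only to baseline assessment. Counting losses as insecure penalises the arm that lost more: with no true effect, 20% of COS refusing and refusers no different from the rest, COS would show 0.80 × 0.50 = 40% secure against 50% in TAU.

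The cost is a reconciliation of the randomisation list with trial IDs, some wording, and a few extra analyses. The estimate may become less certain: best and worst case for the COS rate differ by the share lost, so by 10 to 20 points at 10-20% refusal.
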